### 3.3 Statistical Analyses

#### 3.3.1 Primary analysis

##### Primary outcome:

- Proportion of SARS-CoV-2 positive patients by testing method (RDT vs PCR) and sampling type (saliva vs nasopharyngeal).

##### Study analysis population

All patients recruited will form the study analysis population. All samples will be analysed, except if a patient withdraws his consent after collection and before analysis of his/her sample. If the microbiological test has already been done, we will keep the result in the overall analysis and the patient will still be informed of his/her result due to the fact that it is the public health benefit that prevails over that of the individual.

The proportion of SARS-CoV-2 positive patients (detection rate) and 95% confidence intervals by any method will be presented. Then the detection rate of each method will be compared to that of all other three methods combined (best possible detection rate, true positives).

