| Trial registration:          | This trial is registered in the ClinicalTrials.gov registry and in the Swiss National Clinical trial Portal (SNCTP via BASEC)
FOPH Registration number:                                                                                                                                                                                                                                                                                                                                                                                                                                                                                        |
| Study category and Rationale | 
OClin category A
 
 
- The interventions assessed are the PCR on saliva and the RDT on nasopharyngeal swab against the reference test, which is the PCR on nasopharyngeal swab. RDTs on nasopharyngeal swabs are CE approved and used according to the manufacturer's instructions.
 
 
OClin category C
 
 
- The intervention assessed is the RDT on saliva against the reference test, which is the PCR on nasopharyngeal swab. RDT is CE approved but its use diverges from the manufacturer's instruction.
 
 |
| Clinical Phase:              | 
Diagnostic assessment
 
 
- Compare the detection rates of PCR on saliva, RDT on nasopharyngeal swab, RDT on saliva against PCR on nasopharyngeal swabs
 
                                                                                                                                                                                                                                                                                                                                                                                                                                      |

**Background and  
Rationale:**

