| 
Procedures:
 | 
Patients fulfilling inclusion and exclusion criteria will be recruited consecutively from the two testing sites of Unisanté (Bugnon 44 et Flon) and two testing site in town (Centre medical de la Source and Vidy-Med). After confirmation of inclusion and exclusion criteria (except for anticoagulation that will be asked later), patients will be asked whether they would be willing to provide two saliva samples and one nasopharyngeal swab in addition to that provided for routine testing. After written informed consent, patients will be asked to perform swabbing of the gingiva-buccal fold two times under professional supervision, once for sending to the laboratory to perform PCR, and once for performing the RDT onsite according to the below procedure. They will be taken two nasopharyngeal swabs, one for RDT and one for PCR.
 
The RDTs will be performed and results read according to the manufacturer information (see below).
 
The saliva and nasopharyngeal samples will be handled according to the procedures usually used for nasopharyngeal swabs. Samples will be forwarded to the Institute of Microbiology where they will be analysed by PCR according to the standard procedure (Corman et al 2020, Greub et al 2016, Pillonel 2020).
 
The patient will be considered as positive for SARS-CoV-2 if any of the PCR results or the RDT result on nasopharynx is positive. Indeed, the specificity of these three tests have been shown to be close to 100%. Moreover, in the presence of a suboptimal standard test (PCR on nasopharyngeal swab), it is possible to have higher or differential detection rate with the new tests. The result of the RDT on nasopharynx will be given on the spot because this test has now been validated in a clinical trial (https://www.medrxiv.org/content/10.1101/2020.10.01.20203836v1). The provision of an immediate response may decrease the refusal rate. Since the RDTs are less sensitive than PCR, we will inform patients who receive a negative RDT result that they have to wait for confirmation by PCR analysis before lifting isolation measures. PCR results will be forwarded to the patients using routine channels, the final result being negative if the two PCR and the RDT on nasopharynx are negative, or positive if any of these three tests are positive.
 
Because of problems in RDT availability and need for Swissmedic approval for the Oclin C component, we may start step by step:
 
 
1) PCR on saliva and nasopharyngeal swab
 
2) When RDT are available: PCR on saliva and nasopharyngeal swab + RDT on nasopharyngeal swab.
 
3) When RDT available and Swissmedic approval granted, all four components, namely PCR on saliva and nasopharyngeal swabs, RDT on saliva and nasopharyngeal swab.
 
 |

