
|                                               |                                                                                                                                                                                                                                                                                                                                                                                                                                                                                                                                                                                                                                                                                                   |
|-----------------------------------------------|---------------------------------------------------------------------------------------------------------------------------------------------------------------------------------------------------------------------------------------------------------------------------------------------------------------------------------------------------------------------------------------------------------------------------------------------------------------------------------------------------------------------------------------------------------------------------------------------------------------------------------------------------------------------------------------------------|
| Number of Participants with Rationale: | 
250 SARS-CoV-2 positive patients by any method (RDT on saliva, PCR on saliva, PCR on nasopharynx), which corresponds to ~1250 patients enrolled with
 
 
- 1250 saliva samples for RDT
 
- 1250 saliva samples for PCR
 
- 1250 nasopharyngeal samples for RDT
 
- 1250 nasopharyngeal samples for PCR
 
 
The expected prevalence will be 20% SARS-CoV-2 positive patients by any means (RDT on saliva or nasopharynx, PCR on saliva or nasopharynx)
 
It should be possible to recruit the study subjects relatively easily considering the number of patients who come for testing at Unisanté sites.
 |

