### 2.3 Competent Ethics Committee (CEC) and Competent Authorities (CA)

**Protocol approval.** The principal investigator ensures that approval from an appropriately constituted Competent Ethics Committee (CEC), and Swissmedic is sought for the clinical study OclinC.

**Protocol changes.** No changes are made to the protocol without prior approval from the Sponsor and CEC, except where necessary to eliminate apparent immediate hazards to study participants. Such urgent changes to the protocol due to immediate hazards must be reported to the Sponsor within 48h. According to Oclin art. 37 safety and protection measures which must be taken immediately will be notified to CER-VD.

**Unanticipated risks/benefits.** This is an observational prospective trial that features very little additional risk to the patient. The collection of saliva swabs is innocuous. The standard procedure for nasopharyngeal swab can be accompanied (very rarely) by lesion of the nasal mucosa. It definitely leads to some discomfort, or even pain, for the patient.

Should this study show a case detection rate for SARS-CoV-2 using RDT on saliva of at least 70% of that using the standard method (nasopharyngeal PCR), this new method could be proposed as standard diagnostic testing procedure for testing of ambulatory COVID-19 suspected cases to the cantonal and national health authorities, as well as to the national COVID-19 task force. It should ease the work of the testing teams and lead to less

discomfort for patients, and hence probably higher rate of testing readiness from symptomatic patients. The overall testing expenses per person will also be considerably reduced.

The threshold of 70% has been chosen to take into account that RDT on saliva or PCR on saliva are expected to have an overall detection rate lower than that of naso-pharyngeal PCR, but possibly much higher if patients with very low viral loads (e.g. 1000 copies/ml) are excluded from the analysis (Jacot et al, in press). The detection of the virus in the latter patients is indeed fluctuating strongly from one sample or one moment to another. Moreover, they probably contribute much less to transmission than patients with higher viral loads.

A particular effort will be made to expedite reporting and wide communication, given the global urgency of the COVID-19 testing situation.

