## **2.6 Patient Information and Informed Consent**

### **Recruitment**

- Patients meeting inclusion criteria will be informed about the objectives of the study and given an information sheet. They will be asked for their consent to have a gingivo-buccal and a nasopharyngeal swabbing for PCR, a nasopharyngeal swab for RDT and a gingivo-buccal one for RDT (possibly only two or three swabs, depending on RDT availability and Swissmedic approval). They will be informed about the fact that any positive test (be it from nasopharyngeal PCR, saliva PCR, or nasopharyngeal RDT) will be considered as true positive (and not false positive) because of the excellent specificity of the Ag used for RDT and primers for PCR. This is based also on the principle of precaution since there is no risk of isolating a possible negative symptomatic patient, but there is definitely a public health issue to leave a positive subject being in contact with friends and colleagues.
- No financial compensation will be provided for participation.
- The cost of the routine procedure (nasopharyngeal swab) will be supported by the Direction générale de la santé (DGS) as usual.

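### The primary analysis gives each method a different reference and counts saliva RDT positives as true positives for the other three; separately, the raw detection rate credits saliva RDT with its own false positives

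*Protocol*

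**What the plan says.** **Primary analysis.** In section 3.3.1 the outcome is "Proportion of SARS-CoV-2 positive patients by testing method (RDT vs PCR) and sampling type (saliva vs nasopharyngeal"). Under the analysis population, "The proportion of SARS-CoV-2 positive patients (detection rate) and 95% confidence intervals by any method will be presented", and then "the detection rate of each method will be compared to that of all other three methods combined (best possible detection rate, true positives").

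**Who counts as positive.** The Synopsis (Procedures) states: "The patient will be considered as positive for SARS-CoV-2 if any of the PCR results or the RDT result on nasopharynx is positive". It justifies this by a specificity close to 100% for those three tests. Section 2.6 (Recruitment) says the same: "any positive test (be it from nasopharyngeal PCR, saliva PCR, or nasopharyngeal RDT) will be considered as true positive". Saliva RDT is in neither list. The Synopsis background says there are no saliva data for RDT, and the Study category row says this use departs from the manufacturer's instruction.

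**Other references.** The Study category row reads: "The intervention assessed is the RDT on saliva against the reference test, which is the PCR on nasopharyngeal swab". Section 2.3 sets its criterion as a case detection rate "using RDT on saliva of at least 70% of that using the standard method (nasopharyngeal PCR"). Sections 3.1 and 3.3.2 use the saliva and nasopharyngeal PCR results combined.

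**Recruitment target.** The Synopsis asks for "250 SARS-CoV-2 positive patients by any method (RDT on saliva, PCR on saliva, PCR on nasopharynx"), which leaves out nasopharyngeal RDT. The prevalence line in the same row, and section 3.2, cover all four tests.

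**The concern.** There are two separate problems.

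The first is the reference. Because it changes with the method, the four primary figures share no scale and cannot be ranked against one another. For three of the four methods it includes the one test whose specificity is unknown and which the protocol's own case definition leaves out. Any saliva RDT false positive enlarges the reference and makes the other three tests look worse.

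The second is the numerator. A raw proportion positive does not ask whether the positives are the right patients. A saliva RDT false positive therefore counts as a detection, in section 3.3.1 and in the 70% criterion of section 2.3.

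At 20% prevalence about 1000 of 1250 patients are uninfected, so each 1% of specificity lost adds about 10 false positives to some 250 true cases. Section 2.3 says that reaching 70% could lead to saliva RDT being proposed to the health authorities as a standard procedure, so a distortion of this size matters.

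**Working it through.** **1. The plan's own figure.** 250 / 0.20 = 1250 enrolled. Half-width of the 95% interval: 1.96 × √(0.2 × 0.8 / 1250) = 0.022, which is ±2% after rounding. This reproduces and is not in dispute. The protocol gives no figure for the comparison with the other three methods or for the 70% criterion.

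**2. References side by side.**

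| Place | Reference |
|---|---|
| 3.3.1, for nasopharyngeal PCR | saliva PCR, nasopharyngeal RDT, saliva RDT |
| 3.3.1, for saliva PCR | nasopharyngeal PCR, both RDTs |
| 3.3.1, for nasopharyngeal RDT | both PCRs, saliva RDT |
| 3.3.1, for saliva RDT | both PCRs, nasopharyngeal RDT |
| Synopsis (Procedures), 2.6 | both PCRs, nasopharyngeal RDT |
| 3.1, 3.3.2 | both PCRs |
| 2.3 (70% criterion), Study category | nasopharyngeal PCR alone |

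Only saliva RDT's own reference in 3.3.1 matches the case definition. In the first two roll-out steps not all four tests are done, so the other three do not all exist for those patients.

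**3. Effect on the other three methods.** From the protocol: 250 infected, 1000 uninfected. Assumed, not in the documents: sensitivities of 95% (nasopharyngeal PCR), 90% (saliva PCR), 85% (nasopharyngeal RDT) and 60% (saliva RDT); specificity 100% for the first three; tests independent given infection. Let F = 1000 × (1 − saliva RDT specificity). The reference is 250 × (1 − product of the other three miss rates) + F.

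- Nasopharyngeal PCR: 237.5 / (250 × (1 − 0.10 × 0.15 × 0.40) + F) = 237.5 / (248.5 + F)
- Saliva PCR: 225 / (249.25 + F)
- Nasopharyngeal RDT: 212.5 / (249.5 + F)

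| Saliva RDT specificity | F | Nasopharyngeal PCR | Saliva PCR | Nasopharyngeal RDT |
|---|---|---|---|---|
| 100% | 0 | 95.6% | 90.3% | 85.2% |
| 99% | 10 | 91.9% | 86.8% | 81.9% |
| 97% | 30 | 85.3% | 80.6% | 76.0% |

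The loss is about 3 to 4 points per 1% of specificity, while the true sensitivities do not move. A two-class viral-load model, in which the tests are correlated, gives the same pattern: saliva PCR 89.5, 86.0 and 79.8%.

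**4. Effect of the raw numerator on saliva RDT.** Ratio to nasopharyngeal PCR = (250 × sensitivity + F) / (250 × 0.95).

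| Saliva RDT specificity | Sensitivity 65% | Sensitivity 60% |
|---|---|---|
| 100% | 162.5 / 237.5 = 0.68 | 150 / 237.5 = 0.63 |
| 99% | 172.5 / 237.5 = 0.73 | 160 / 237.5 = 0.67 |
| 97% | 192.5 / 237.5 = 0.81 | 180 / 237.5 = 0.76 |

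The 70% line is 0.70 × 237.5 = 166.25 positives. It is crossed in expectation with 3.75 false positives if sensitivity is 65% (specificity 99.6%), and with 16.25 if it is 60% (specificity 98.4%).

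Probability that one trial shows a ratio of at least 0.70, simulated with the two tests drawn independently given infection: at 99% specificity, 77% if sensitivity is 65% but 24% if it is 60%. At 100% specificity it is 32% and about 2%, from sampling variation alone.

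**5. Which part causes the lift.** Take 60% sensitivity and 97% specificity. Against the fixed three-test reference (250 × (1 − 0.05 × 0.10 × 0.15) = 249.8) the raw ratio is still 180 / 249.8 = 72.1%. If only positives who are also reference-positive are counted, it is 60.0% at every specificity. Fixing the reference alone is therefore not enough; the counting rule must change too.

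**The case against.** **The lift over 70%.** A reader might infer that the shifting reference itself carries saliva RDT over its 70% criterion. The documents do not support this. The criterion is set against nasopharyngeal PCR alone, and saliva RDT's own reference in 3.3.1 excludes its own positives. Any lift comes from the raw numerator.

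**Concordance may be intended.** Calling the reference true positives, and the interim wording about patients detected by PCR, can be read as counting only concordant positives. Under that reading there is no lift. This stands as an ambiguity, but the stated outcome and definition are raw proportions, and section 2.3 compares rates. Concordant counting would not remove saliva RDT from the other methods' reference.

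**Leaving out the index test is defensible.** It avoids judging a test against itself, and the Synopsis argues that nasopharyngeal PCR alone is a suboptimal standard. Both points are fair. They justify a composite reference, but not including a test of unknown specificity in it. The Procedures and Recruitment text mainly governs results given to patients, yet its specificity argument applies equally to the analysis.

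**The sizes are assumed.** This stands. Appendix 2 lists specificities of 99.40% and 99.68% for two of the trial's brands, but on nasopharyngeal swabs, which does not settle saliva. At 100% neither false-positive effect exists.

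**Ratios above 100%.** A reader might also infer that nasopharyngeal PCR must exceed 100% of its own reference. It need not: with perfect specificity it is 95.6% under independence and 102.1% in the two-class model.

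**Policy.** Nor does reaching 70% automatically trigger a recommendation; section 2.3 says only that the method could be proposed.

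**Conclusion.** The point holds as two separate defects.

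- **Reference.** Section 3.3.1 uses four different references and, for three methods, treats saliva RDT positives as true positives, against the Synopsis and section 2.6. Sections 2.3, 3.1 and 3.3.2 add further references. This inconsistency is in the text and needs no assumption. Its numerical effect, a loss of about 3 to 4 points per 1% of saliva RDT specificity for each of the other tests, rests on 20% prevalence, a specificity below 100% and the assumed sensitivities.
- **Numerator.** As defined, the detection rate counts saliva RDT's own false positives as detections. Whether that decides the 70% result depends heavily on values the documents do not give, as the gap between 77% and 24% shows. It should be stated as a risk with its range, not as an expected outcome.

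The sample size of 1250 is not affected.

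**What to change.** 1. In sections 3.1, 3.3.1 and 3.3.2, and in the 70% criterion of section 2.3, name one fixed reference that excludes saliva RDT. Composite PCR (either PCR positive) is the natural choice because 3.1 and 3.3.2 already use it. Add the three-test definition from the Synopsis and section 2.6 as a sensitivity analysis.
2. For each RDT, report the share of reference-positive patients who are RDT positive, with a 95% confidence interval. Report RDT-positive, reference-negative patients separately and not as detections.
3. Compare the two PCRs by their paired 2×2 table, since both form part of the reference.
4. Keep the target of 250 positives, but reconcile the two test lists in the Synopsis participant row.

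**Cost.** No new data: section 5.1.1 already records all four results separately. The wording needs a protocol amendment. Genuine RDT-only cases leave the headline figure but stay reported. The sponsor should also confirm that 70% is still the intended level once the measure changes: in the example with 60% sensitivity and perfect specificity, a raw ratio of 0.63 to nasopharyngeal PCR becomes a share of 60%.

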##### Secondary outcome:

- Viral loads (number of copies/ml) of SARS-CoV-2 by sample type, namely PCR saliva and PCR nasopharyngeal swabs

Viral loads will be compared between the two sample collection methods using the Kruskal-Wallis rank test. Pearson correlation coefficient will also be used to compare viral load values using the two methods.

Stratified analysis of detection rates will be performed. Detection rates of the two RDT methods will be calculated according to two virus load categories ( $<36$  Ct value,  $\geq 36$  Ct value)

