In addition, Rapid Diagnostic Tests for the detection of SARS-CoV-2 antigens have been developed using nasopharyngeal swabs and have shown very high sensitivity against PCR, ranging from 93% to 98% when based on laboratory validation. [see summary table from [name] (unpublished) in Appendice 2 and Kruger et al <https://www.medrxiv.org/content/10.1101/2020.10.01.20203836v1>]. This method offers the considerable advantage to inform the patient of the test result on site, and allow the provision of appropriate recommendations on the spot of testing. The studies performed so far have been conducted using nasopharyngeal samples only. There are no data with saliva yet. It is expected that the RDT would also work on the saliva. Even if slightly less sensitive due to the fact that it detects antigens and not multiplied RNA as PCR does, RDT on saliva could better serve the public health goal to test widely and quickly and have ultimately more COVID cases detected and isolated, and hence reduced transmission.

To investigate the case detection rates of both PCR on saliva and nasopharynx and RDT on nasopharynx and saliva, we intend to take four samples, two swabs on saliva, one for RDT and one for PCR, and two swabs on nasopharynx, one for RDT and one for PCR. Patients who have at least one of the common symptoms and who consent to such a procedure will be recruited to compare the four results. Our primary objective is to compare the case detection rates for SARS-CoV-2 of the four testing methods (two sampling types and two test types). Since we may not have RDT and Swissmedic approval at the very start of the trial, we may introduce the different new tests step by step.

To be precise, we write 'saliva sample', but precisely we mean gingivo-buccal swab sample, and this thereafter in the document.

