| 
Intervention:
 | 
In spite of the difficulty to purchase antigen RDT, we were able to receive tests from three different brands that are all CE approved. In order to test the three different brands, and therefore have stronger generalization ability, we will rotate RDT brand use after 33 patients recruited. We started with the RDT from Roche (Standard Q COVID-19) (https://www.roche.com/media/releases/med-cor-2020-09-01b.htm), and then switch to RDTs from Abbott (Panbio COVID-19 Ag) (https://www.globalpointofcare.abbott/en/product-details/panbio-covid-19-ag-antigen-test.html) and then to those from AAZ-LMB (COVID-VIRO) (http://www.covid19aaz.com/). After 99 patients, we will start the cycle again and so on.
 
Saliva sample collections will be performed following the guidance published in Ott et al (2020) and Kojima et al (2020). Instead of collecting only saliva in a tube, the patient will perform him/herself a swab of the gingiva-buccal fold, under the supervision of a healthcare worker. A pilot test is ongoing at Unisanté to ensure appropriateness of swab type and procedure. The results of the first 10 positive patients done as a pilot show perfect concordance between PCR results on saliva and nasopharyngeal samples, with 1-3 log viral load less in saliva. Now that we got the RDT, we will follow the pilot on a few samples for RDT analysis on saliva.
 
No coughing or sniffing prior to sample collection is required. Ideally, water should be avoided 10 minutes prior to collection. Other drinks, food, and nasal sprays should be avoided 20 minutes before sample collection.
 
The health care worker must wear a personal protection equipment (at minimum, mask and gloves) prior to contact with the patient. The patient must clean his/her hands using alcohol-based sanitizer or soap and water (no fragrances).
 
The health care worker should verify all collection material labelling (at minimum, patient name/identifier and date and time of collection) with the patient. While preparing collection materials, he/she directs the patient to begin pooling saliva in his/her mouth.
 
If the RDT are available and Swissmedic granted, the following sampling procedure will be performed:
 
 
1) A first swab will be done on saliva by the patient using the 4 zones (gingiva-buccal fold left and right, tongue and palate) for 30 seconds to perform PCR (see video from 1:14 https://coronavirus.delaware.gov/drive-thru-testing-instructions-for-curative-test-english/).
 
2) The second swab will be on saliva collection. The health care worker will open the RDT kit, give the swab to the patient that will pass it for 30 seconds in the 4 zones of the gingiva-buccal fold. The health care worker will perform immediately the RDTs according to the manufacturer instruction as above, e.g (Standard Q COVID-19) (Roche/SD Biosensor : https://www.youtube.com/watch?v=mBdaOHJWxI4).
 
3) The third swab will be done on nasopharyngeal fluid by the health worker to perform PCR (reference test).
 
4) The fourth swab will be done on nasopharyngeal fluid by the health worker to perform the RDT. He will perform immediately the RDTs according to the manufacturer instruction.
 
 |

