## **5. QUALITY ASSURANCE AND CONTROL**

### **5.1 Data handling and record keeping / archiving**

#### **5.1.1 Case Report Forms**

All protocol-required information will be collected directly from a tablet and entered in REDCAP. Other source documents if necessary will be stored securely. Few variables will be collected, namely ID number, phone number, date of birth, date, sex, duration of symptoms, fever (Y/N), cough (Y/N), anosmia a Y/N), ageusia (Y/N), anticoagulation (Y/N), PCR saliva test result (positive/negative and Viral loads), PCR nasopharyngeal test result (positive/negative and viral loads), RDT nasopharyngeal test result, RDT saliva test result,

Only the Sponsor, PIs, investigators, site coordinators and medical professionals will be allowed to access the source documents and database.

Once identifying information is no longer required for the basic functioning of the trial (i.e. the requirement to identify patient, and telephone for result return), all eCRFs will be strictly anonymised and only the participant number in combination with year of birth will remain.

This identifying information that is removed from eCRFs at the end of participant follow-up will be transferred to a separate secured file which is independent from the eCRFs. And this will be made available only under request to the PI (if the request pertains to pharmacovigilance monitoring, quality assurance reviews, audits or a medical concern of the patient, with the patients consent).

This procedure will be identical for the two new sites, namely the Centre Médical de la Source and Vidy-Med. Indeed, the procedures for result transmission to the patients are handled by the same laboratory for Unisanté and Vidy-Med (Laboratoire de microbiologie). The anonymization and coding can thus be performed in the same manner in all sites.

Only the Sponsor, Investigators, the CER-VD and regulatory authorities will have access to the records.

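### Saliva and nasopharyngeal viral loads from the same patient are compared with Kruskal-Wallis, a test for independent groups, which makes this secondary comparison conservative

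*Protocol*

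**What the plan says.** Section 3.3.1 of the protocol, under Secondary outcome, defines the outcome as "Viral loads (number of copies/ml) of SARS-CoV-2 by sample type, namely PCR saliva and PCR nasopharyngeal swabs". It then fixes the method: "Viral loads will be compared between the two sample collection methods using the Kruskal-Wallis rank test". The next sentence adds: "Pearson correlation coefficient will also be used to compare viral load values using the two methods".

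The rest of the protocol shows that the two viral loads belong to one person:

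- The Background in the synopsis describes the samples per patient as "two swabs on saliva, one for RDT and one for PCR, and two swabs on nasopharynx, one for RDT and one for PCR".
- The Procedures row lists three start-up steps. The first is already "PCR on saliva and nasopharyngeal swab", and the other two only add rapid tests.
- The Intervention row lets a patient decline the second nasopharyngeal swab. In the four-swab sequence that is the swab for the rapid test, so both PCR samples remain.
- Section 5.1.1 lists among the variables collected for each patient "PCR saliva test result (positive/negative and Viral loads), PCR nasopharyngeal test result (positive/negative and viral loads".

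The Intervention row also reports the pilot on the first 10 positive patients, "with 1-3 log viral load less in saliva".

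**The concern.** Kruskal-Wallis with two groups is the Wilcoxon rank-sum test. Its null variance is derived for values from unrelated people. Two samples taken from one infected person at one visit will normally be positively correlated: a patient with a high load in the nasopharynx tends to have a higher load in saliva. The unpaired test leaves that between-patient spread in its reference variance instead of removing it by differencing, so its p-values are too large.

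What is at stake is the efficiency of a secondary comparison, and whether the reported result answers the useful question of how many log10 copies/ml fewer saliva carries in the same patient. The planned Pearson correlation does use the pairs, but it measures association. If every saliva load were multiplied by the same factor, the correlation would not change, either in copies/ml or on the log scale. It therefore cannot show the size of the deficit.

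**Working it through.** **Plan's own figure.** The protocol gives no sample size, power or precision for the viral-load comparison, so there is nothing to reproduce. Its one computed figure, a precision of ±2% on the detection rate, concerns the primary outcome and does not bear on this point.

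**Inputs from the protocol.** 250 positive patients (section 3.2), both PCR samples from each patient, and a pilot deficit of 1-3 log in saliva.

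**Assumptions not in the protocol.** Bivariate normal log10 loads, SD 1.5 log10 in each sample type, within-patient correlation ρ from 0 to 0.7, and two-sided α of 0.05. Taking 250 pairs assumes that every positive patient yields two usable loads, so it is a best case.

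**Step 1: type I error by formula.** With no true difference, the variance of the rank-sum statistic under pairing, divided by the variance the test assumes, is in large samples 1 − ρs. Here ρs is the Spearman correlation, and for bivariate normal data ρs = (6/π)·arcsin(ρ/2). The true type I error is therefore 2·[1 − Φ(1.96/√(1 − ρs))].

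| ρ | ρs | √(1 − ρs) | 1.96/√(1 − ρs) | True type I error |
|---|---|---|---|---|
| 0.3 | 0.288 | 0.844 | 2.32 | 2.0% |
| 0.5 | 0.483 | 0.719 | 2.72 | 0.6% |
| 0.7 | 0.683 | 0.563 | 3.48 | 0.05% |

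**Step 2: type I error by simulation.** 10,000 data sets per setting, 250 pairs, no true difference.

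| ρ | Kruskal-Wallis | Signed-rank |
|---|---|---|
| 0 | 5.0% | 5.1% |
| 0.3 | 2.0% | 4.9% |
| 0.5 | 0.7% | 5.3% |
| 0.7 | 0.08% | 4.9% |

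The simulation agrees with the formula. The result hardly depends on the number of pairs: with 40 pairs, Kruskal-Wallis rejects in 2.2% / 0.6% / 0.08% at ρ 0.3 / 0.5 / 0.7. The planned test holds its nominal level only at zero correlation.

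**Step 3: power by simulation.** 250 pairs, SD 1.5 log10. Each cell gives Kruskal-Wallis, then signed-rank.

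| ρ | 0.3 log10 | 0.5 log10 | 1 log10 |
|---|---|---|---|
| 0.3 | 60% / 74% | 98% / 99% | 100% / 100% |
| 0.5 | 62% / 87% | 99% / 100% | 100% / 100% |
| 0.7 | 66% / 98% | 100% / 100% | 100% / 100% |

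The loss is large for a difference of 0.3 log10, which is 0.3/1.5 = 0.2 SD, and nearly gone by 0.5 log10.

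**Step 4: the pilot scenario.** The lower end of the pilot range is 1 log, where both tests have 100% power. This does not rest on the choice of SD. Power depends on the difference divided by the SD, so 1 log at SD 3 equals 0.5 log at SD 1.5 (both 0.33 SD), where Kruskal-Wallis still has about 98% power or more.

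**Step 5: precision of the paired estimate.** The 95% half-width for a mean within-patient difference is 1.96·SD·√(2(1 − ρ)/n). With SD 1.5 and n = 250 this is 0.220 / 0.186 / 0.144 log10 at ρ 0.3 / 0.5 / 0.7. A paired analysis could therefore place the deficit to within roughly 0.2 log10.

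**The case against.** The strongest reply is that nothing important turns on this test. Viral load is a secondary outcome. The primary hypothesis, the 70% threshold in section 2.3 and the interim rules in section 3.3.2 all rest on detection rates. With a deficit of 1-3 log, the planned test would reject anyway. All of this stands, and it limits the severity. It does not make the named test right, and an unseen analysis plan does not excuse it, because the protocol itself fixes the method. Section 3.3.3 allows modifications but corrects nothing.

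A reader might infer more than the protocol supports:

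- *False positives.* With positive correlation the type I error is below 5%, so the planned test does not raise the risk of falsely declaring a difference.
- *Wrong error bars.* The protocol plans no interval or error bar for viral load. An interval that ignored the pairing would be too wide, but none is proposed.
- *Changed conclusions by rapid-test brand or at low viral load.* The protocol plans no viral-load comparison in such subgroups. Brand rotation concerns the rapid tests, whereas viral loads come from PCR, and the Ct strata in section 3.3.1 apply to detection rates.
- *A missing effect estimate as a fault in itself.* A protocol may leave effect measures to the analysis plan. The estimate is what a paired analysis adds; the fault is the choice of test.

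**Conclusion.** Wrong as written, minor to moderate: it should be corrected, but it does not threaten the trial. A test for independent groups is named for paired data.

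That the test is conservative rests only on positive within-patient correlation. The type I error of about 2% / 0.7% / 0.1% rests on assumed correlations of 0.3 / 0.5 / 0.7. The power loss for a 0.3 log10 difference (14, 25 and 32 percentage points) rests in addition on 250 usable pairs and an SD of 1.5 log10. None of these correlations or SDs is given in the protocol.

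If the pilot deficit is confirmed, the finding that saliva carries less virus will be the same under either test. What changes is that the deficit can be reported as a within-patient quantity with a valid interval. The primary analysis is untouched.

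**What to change.** In section 3.3.1, under Secondary outcome:

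- Replace the Kruskal-Wallis test with the Wilcoxon signed-rank test on the within-patient difference in log10 copies/ml, saliva minus nasopharynx, among patients positive by at least one PCR. State the log scale, because the signed-rank test, unlike Kruskal-Wallis, depends on it.
- Report the Hodges-Lehmann median difference with its 95% CI.
- Fix a rule in advance for a sample undetectable by PCR, since the log of such a load is undefined. One option is to set it to the assay's detection limit. When only saliva is undetectable, this understates the deficit in that patient.
- Add a sensitivity analysis restricted to patients positive on both samples.
- Keep the Pearson correlation as a description of association only.

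The cost is a few sentences. Both viral loads are already collected for each patient, so no new data and no added patients are needed.
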